#### Outcomes

All outcomes are described in detail in Table 2. The primary outcome is the incidence of RD.

**Table 2 Tab2:** Primary and secondary outcomes

	**Measuring instruments/definitions**
**Primary outcomes**	
Incidence of RD	Patients with radiation-induced dermatitis (RD)
Evaluation of the skin lesion (RD)	(1) remains the same or worsens; (2) partial improvement; (3) total improvement or complete cure
**Secondary outcomes**	
Onset and duration of RD	Time of onset and duration of post-radiation dermatitis
Toxicity in patients’ irradiated skin	Common toxicity criteria of the cooperative group for skin suggested by the RTOG Foundation (https://www.rtog.org) [18]
Discomfort and pain concerning symptoms and signs related to dermatitis	Degree of skin discomfort caused by radiation. Subjective assessment and quantification by the patient on an ordinal scale (0 to 10) Pruritus, pain, itching, or peeling of the skin
Quality of life	Quality of life of patients with skin conditions Skindex-29 questionnaire [19]

In addition, secondary outcomes include the level of toxicity in patients’ irradiated skin. It will be assessed according to the common toxicity criteria of the cooperative group for skin suggested by the RTOG Foundation (https://www.rtog.org) [18] according to which toxicity is classified into five levels: 0 for no toxicity or no change; 1 for scattered macular or papular rash or erythema that is asymptomatic; 2 for scattered macular or papular rash or erythema with pruritus or other associated symptoms; 3 for symptomatic generalized macular, papular, or vesicular rash; and 4 for exfoliative dermatitis or ulcerative dermatitis.

The assessment of discomfort and pain concerning symptoms and signs related to dermatitis is based on the subjective assessment and quantification by the patient on an ordinal scale (range 0 to 10), the Visual Analogic Scale (VAS), answering the following question: What score would you rate from 0 (where 0 is the situation where you do not feel symptoms such as pruritus, pain, itching, or peeling of the skin) to 10 (where 10 is the situation where you notice the most symptoms) to your skin problem where do you have the lesion?

Quality of life will be assessed by completing the Skindex-29 questionnaire. Skindex-29 is a self-administered questionnaire to measure the quality of life of patients with skin conditions every 4 weeks, consisting of 29 items. The Spanish version of Skindex-29 has been validated [19].

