## Introduction

### Background and rationale

Radiotherapy, the use of high-energy rays to either kill cancer cells or treat some benign tumors, is undoubtedly a positive intervention. However, as the primary mode of action in radiotherapy treatment is killing cells to prevent replication, other non-cancerous cells may be affected. For example, up to 85% of patients will experience some form of skin reaction, ranging from local erythema to moist desquamation. Such reactions are distressing and painful for the patient, and if severe enough, they may warrant treatment discontinuation [1].

According to the MSD manual [1], general treatment of dermatitis includes supportive care of cosmetic type (such as moisturizers, dressings, and antihistamines for itching), topical corticosteroids, and sometimes antibiotics or other drugs, or ultraviolet light therapy. Treatment of dermatitis depends on the cause and the specific symptoms. Depending on the severity of the process, this therapeutic ladder can be gradually climbed to treat the milder symptoms to the more severe and chronic ones.

According to the Society and College of Radiographers [2], topical emollients are commonly used to prevent radiation-induced dermatitis (RD) or to provide comfort for patients once a reaction has occurred. As radiation damages the basal cell layer of the skin, the normal desquamation of cells and growth of replacement cells are interrupted, and skin dehydration occurs. Topical emollients are used to hydrate the skin and ameliorate feelings of itching and soreness.

From this point on, all treatments are based on drugs and not cosmetics. However, the latter will serve on the following therapeutic steps to supplement hydration and soothe irritation and pruritus. Among these natural products are aloe vera and chamomile [3–5]. These agents, qualified as cosmetics, have been used to treat iatrogenic RD to alleviate the symptoms and signs of this condition [6–9]. Other studies report using other cosmetic therapies to relieve symptoms and signs of dermatitis [10, 11].

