#### Eligibility criteria

Inclusion criteria are as follows: patients aged 18 years or older diagnosed with breast cancer and who are going to start radiation therapy with a radical intention on the affected breast, by the hypofractionated scheme with integrated boost (40.05 Gy with integrated boost, 48 Gy, in 15 sessions), coming from centers involved in the project or that can be followed up by a participating primary care professional and that sign an informed consent.Exclusion criteria are as follows: patients with dermal lesions or invasive skin cancer or distant metastases; history of connective tissue disorders; severe mental disorder (dementia, drug addiction, etc.); history of hypersensitivity reaction to any of the ingredients in the study cream; history of severe/extensive burn, moisture, erosion, or drainage in the treatment area; or participants involved in other clinical trials within that month.

Fourteen collaborating clinical researchers (5 oncologists, 8 GP, and one primary care occupational therapist) will perform the therapeutic intervention to be tested.

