#### Interventions

Once the patient has been included in the study and allocated to one of the two groups, the radiation oncologists will collect demographics and existing pathologies and perform an initial assessment of the skin to be irradiated before the start of radiation therapy. The radiation oncologist will administer the patient a Quality-of-Life Assessment Questionnaire (Skindex-29) [19] and inform the family physician of the patient’s details, identification code, and probable date of initiation of radiation therapy so that the family physician can contact the patient prior to the start of the treatment to schedule follow-up visits.

At each follow-up visit after sessions 5, 10, and 15 and 1 week after completion of radiation therapy, the family physician will perform the following actions:

Evaluate patients’ irradiated skin according to the common toxicity criteria of the cooperative skin group suggested by the RTOG Foundation (https://www.rtog.org) [18].Likewise, patients presenting with dermatitis will be asked to assess and quantify the discomfort and pain related to dermatitis symptoms and signs on an analog ordinal scale (from 1 to 10).Complete the Skindex-29 Quality of Life Questionnaire [19] (https://www.bibliopro.org/buscador/294/cuestionario-dermatologico-de-calidad-de-vida-skindex-29).Record adverse events (AE): Possible AE will be evaluated and reported during the study, and their causal relationship with the components of the cream will be assessed. If an adverse reaction is found, the researcher will evaluate the intensity and frequency of each episode and decide whether or not additional treatments are needed. These side effects will be notified to the Andalusian Pharmacovigilance Center through the yellow card alert system. If the physician considers it appropriate, the patient will be withdrawn from the study.

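### The toxicity scale does not say where desquamation is graded, leaves *generalized* undefined for a single irradiated breast, and conflicts with the Introduction's description of the same scale

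*Protocol article*

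**What the plan says.** The Outcomes section defines toxicity of the irradiated skin, a secondary outcome in Table 2, on five levels. Level 0 is no change. The others are:

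- Level 1: "1 for scattered macular or papular rash or erythema that is asymptomatic".
- Level 2: "2 for scattered macular or papular rash or erythema with pruritus or other associated symptoms".
- Levels 3 and 4: "3 for symptomatic generalized macular, papular, or vesicular rash; and 4 for exfoliative dermatitis or ulcerative dermatitis".

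Three other places bear on how these levels work:

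- Interventions: at each follow-up visit the family physician is to "Evaluate patients’ irradiated skin according to the common toxicity criteria of the cooperative skin group suggested by the RTOG Foundation".
- Eligibility criteria: patients are about to start "radiation therapy with a radical intention on the affected breast".
- Background and rationale: "up to 85% of patients will experience some form of skin reaction, ranging from local erythema to moist desquamation".

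Later in the Introduction the same reference (number 18) is cited for a scale of five degrees. There, categories 1 and 2 are illustrated by skin atrophy, hair loss, depigmentation and telangiectasia, and are called treatable with cosmetics.

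**The concern.** A severity scale should give each lesion the protocol expects one place. Here the severe end of the expected range, moist desquamation, is named in the Introduction and in none of the levels. The step from 2 to 3 turns on a word about extent, *generalized*, that is not defined for a field limited to one breast. The two accounts of the scale also differ in content.

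This grade is the trial's only graded measure of how severe a lesion is, because the other lesion item in Table 2 records change only (same or worse, partly improved, cured). It is taken at all four visits. The raters are eight general practitioners and one occupational therapist, with some patients followed in the radiation oncology service instead. If the same lesion gets different grades from different raters, the distribution of grades, and above all the proportion at grade 3 or above, partly reflects who examined the patient.

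**Working it through.** **1. Lesions against levels.** Each reaction is read against the wording in the Outcomes section.

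| Reaction in the irradiated breast | Levels the wording allows | Why |
|---|---|---|
| Itching erythema over the whole breast | 2 or 3 | 2 if *scattered* qualifies only the rash; 3 if *generalized* means extent within the field and erythema counts as macular rash |
| Dry desquamation, no complaint | 1, 2 or 4 | 1 as nearest symptom-free level; 2 if peeling is an associated symptom, as the discomfort question treats it; 4 if called exfoliative |
| Painful moist desquamation, no ulcer | 2 or 4 | 2 by its symptoms; 4 if called exfoliative |
| Ulceration | 4 | Named in level 4 |

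Only the last row has a single answer.

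**2. The two descriptions of the scale.** For categories 1 and 2 the Introduction lists atrophy, hair loss, depigmentation and telangiectasia. The Outcomes section lists scattered rash or erythema without and with symptoms. The two lists share no item, although both cite reference 18. Neither places desquamation.

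**3. Sample size, to see whether it is touched.** Inputs from the Sample size section: 46.7% and 78.6%, alpha 0.05 (two-sided assumed), power 80%, loss 20%.

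- Mean rate = (0.467 + 0.786)/2 = 0.6265; difference = 0.319.
- n = [1.960 × √(2 × 0.6265 × 0.3735) + 0.842 × √(0.467 × 0.533 + 0.786 × 0.214)]² / 0.319² = 34.9, so 35 per arm.
- 35/0.80 = 43.75, so 44 per arm and 88 in total, as the protocol states.

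The toxicity grade does not enter this calculation.

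**4. Possible size of the effect on the grade.** The documents do not give the share of dermatitis patients who reach desquamation, so it is assumed: 10–20% with Alantel and 20–40% with control.

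- Patients with dermatitis at 35 per arm: 35 × 0.467 = 16.3 and 35 × 0.786 = 27.5.
- With desquamation: 1.6 to 3.3 with Alantel, 5.5 to 11.0 with control.

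Simulated power of a two-sided Mann-Whitney test at 0.05 (35 per arm, 4,000 trials, Monte Carlo standard error about 0.6 points at 80% power). The remaining dermatitis patients are split equally between asymptomatic and symptomatic erythema.

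| Desquamation share, Alantel vs control | Ranked above symptomatic erythema | All scored 2 | Scattered equally over 1, 2 and 4 |
|---|---|---|---|
| 10% vs 20% | 79% | 76% | 73% |
| 10% vs 40% | 92% | 84% | 78% |
| 20% vs 40% | 86% | 81% | 76% |

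The loss is 3 to 8 points when all desquamation is scored 2, and 6 to 14 points when it is scattered. If every rater used grade 4, the ranking would be that of the first power column and the loss would be zero.

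**The case against.** A reader might infer that the scale has no level at all for desquamation, so that the worst reactions are scored as mild or cannot be scored. The documents do not support that. Exfoliative and ulcerative dermatitis at level 4 carry no requirement to be generalized, and a rater may reasonably put moist desquamation there. Nor is grade 3 shown to be out of reach. The levels are stated for irradiated skin, so *generalized* can be read as extent within the field.

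A reader might also infer that a harmful effect would go unseen. It would not, because worsening is a category of the lesion evaluation in Table 2, and signs, discomfort and adverse events are recorded at every follow-up visit. Nor does the fault reach the primary outcomes. The Abstract speaks of mild dermatitis, but Table 2 attaches no toxicity grade to either primary outcome.

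The power figures rest on assumed shares with a benefit on desquamation built in, on an arbitrary equal scatter, and on a test that the Statistical methods section does not name for this outcome. The trial is also aimed at mild, early dermatitis, which makes the upper levels less central. Finally, the article is a condensed text, and the case report form or rater instructions may settle the placement.

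These points limit the consequence but leave the wording problem standing. Readings under which everything fits are possible, but the text does not choose among them, and nine raters need not choose alike. The conflict between the Introduction and the Outcomes section is on the page whatever the form says. Whether either description matches the cited criteria cannot be checked from the documents.

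**Conclusion.** The point holds as a measurement ambiguity in a secondary outcome. Moist desquamation can be graded 2 or 4, dry desquamation has no determinate level, the boundary of grade 3 is undefined within one breast, and two sections describe the scale differently under one reference. The primary outcomes and the sample size are unaffected.

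The power loss of about 3 to 14 points is illustrative only, because the desquamation shares and scoring patterns are assumptions, and it is nil if raters consistently use grade 4. If blinding held, inconsistent grading would mainly blur a difference rather than create one. The more practical harm is to interpretation: a reported proportion at grade 3 or above would depend in part on rater choice. This should be corrected, but it does not threaten the trial's main result.

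**What to change.** Reconcile the Introduction and the Outcomes section to one scale, graded within the irradiated field. State at which level dry and moist desquamation fall, and either remove *generalized* or define it as extent within that field. Several wordings would serve; what matters is that each expected lesion has one level.

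Trial status says the study concluded in June 2023, so new wording cannot change how patients were examined. Before unblinding, regrade under the reconciled wording from the recorded symptoms and signs of dermatitis (Table 1), by assessors who do not know the group, and document the rule. Table 1 does not list which signs were captured, so this may be possible for only some visits. Where the records are too thin, report the ambiguity with the results and draw no conclusion from the proportion at grade 3 or above.

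The cost is some regrading work and less direct comparability with sources that used the rash wording. No new visits or examinations are needed.

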#### Sample size

Taking as reference those values provided in a previous study [20], the expected occurrence rate of RD (primary outcome variable) would be 46.7% in EG and 78.6% in CG, respectively; with a 1:1 allocation, accepting an alpha risk of 0.05 (5%) and a beta risk of 0.20 (20%), and assuming a follow-up loss rate of 20%, 88 eligible patients (44 in each group) are needed (calculations performed with the Granmo software version 7.12 in: https://www.imim.cat/ofertadeserveis/softwarepublic/granmo/, sample size for two independent proportions).

#### Recruitment

Patients from both groups will be recruited at the Radiation Oncology Unit of the Reina Sofia Hospital (Cordoba, Spain). They will be followed up by family physicians and a primary care occupational therapist after sessions 5, 10, and 15 of radiotherapy and 1 week after the end of the treatment. Those in the EG will be given the test cosmetic cream, while those in the CG will receive a moisturizing cream. The moisturizing cream will be very similar to that of the Alantel, both in color, container, weight, and smell, and will be manufactured by the laboratory producing Alantel.

## Assignment of interventions: allocation

### Sequence generation

The same number of participants will be assigned to the two study groups using the block randomization procedure. The assignation will be performed by one of the investigators, an expert in statistics, who will remain blind to the allocation of subjects during the statistical analysis. The random allocation sequence of eligible patients to the EG or the CG will be generated using EPIDAT version 4.1. Allocation will be implemented by submitting a written document with the randomized allocation sequence to be followed by each oncologist. Once the sequence for allocating the 88 patients to each group is generated prior to the start of the field phase, this will be distributed among the participating oncologists to prevent assigning the same code to two different patients. The numbers from 1 to 17 will be assigned to the oncologist one, from 18 to 32 will be assigned to the oncologist two, and so on. In this way, each oncologist will know which number and to which group each patient should be assigned, generating an alphanumeric code.

The alphanumeric codes will be constructed according to the following order: number of the recruited patient (01, 02,…); assigned group (A or B); oncologist responsible for the case (1–5); primary care physician (1–9).

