#### Who will take informed consent?

The radiation oncologists will collect the informed consent during the recruitment process. In the informed consent form, in case the recruited patients consent to participate, they will be asked if they accept the use of their data, even if they decide to drop out.

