#### Withdrawals or dropouts from the trial

Those patients meeting the selection criteria and willing to participate in the study who could not do so because they do not have the means to travel to the primary care center that corresponds to them will be offered the possibility of being followed up in the radiation oncology service. In addition, possible deviations from the protocol, discontinuities in visits, withdrawals, losses, and their reasons will be collected in a registry of incidents occurring during the follow-up of patients. In case the patient expresses her request to drop out of the trial for any reason, she will be withdrawn from the trial. Likewise, those patients who, by clinical criteria, the field investigator considers their discontinuation will be withdrawn. Patients lost to follow-up due to not attending the visits, death, and other reasons evaluated by the research team will also be recorded.

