## Assignment of interventions: blinding

This is a triple-blind study, where neither the investigator responsible for the intervention nor the patients included in the study will know at any time whether they receive Alantel cream or control moisturizing cream. The statistician in charge of the analysis will also remain blind. The product bottles will be similar in appearance, containing the active substances for the EG and a harmless moisturizing substance for the CG. The company making the Alantel cream will also prepare and provide the moisturizing cream.

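### Recruiting oncologists hold the A/B list for their number range and the letter sits in the patient code, so allocation is not concealed and the blind is fragile.

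*Protocol article*

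**What the plan says.** All of the following is in the protocol article.

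- **Sequence generation**, on how the sequence reaches the recruiters: "Allocation will be implemented by submitting a written document with the randomized allocation sequence to be followed by each oncologist". On timing, the sequence for the 88 patients is "generated prior to the start of the field phase, this will be distributed among the participating oncologists". On how it is split: "The numbers from 1 to 17 will be assigned to the oncologist one, from 18 to 32 will be assigned to the oncologist two"; the other three oncologists get the later ranges in the same way. The stated result is that "each oncologist will know which number and to which group each patient should be assigned".
- **Who will take informed consent?** "The radiation oncologists will collect the informed consent during the recruitment process". The people holding the lists are the people enrolling.
- **Sequence generation**, on the patient code: after the patient number it contains "assigned group (A or B); oncologist responsible for the case (1–5); primary care physician (1–9").
- **Interventions:** the oncologist makes the initial skin assessment once the patient has been included and allocated, then sends the identification code to the family physician, who grades the irradiated skin at each follow-up visit.
- **Data collection and management:** an alphanumeric code identifies each patient for the analysis.
- **Assignment of interventions: blinding:** "neither the investigator responsible for the intervention nor the patients included in the study will know at any time" which of the two creams is received. The analysing statistician is also to stay blind, and the bottles look alike.

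The article describes no step that hides the next assignment until a patient is enrolled.

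**The concern.** Concealment and blinding are separate safeguards. Concealment keeps the recruiter from knowing the next assignment until the patient is irrevocably in the trial. Blinding keeps people from knowing the treatment afterwards. The article provides for the second and gives up the first: a recruiter who comes to believe that one letter does better, rightly or wrongly, can choose whom to enrol next and in what order. Several exclusion criteria (existing dermal lesions, a history of moisture or erosion in the treatment area, severe mental disorder) need judgement, which leaves room for this. Baseline skin is also recorded with the letter known.

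The second weakness is that only two labels serve 88 patients and the label travels with the patient code. The primary outcome is a clinician's judgement of a skin reaction, so an assessor who has decoded the letter can lean in grading. Selection bias at entry and detection bias at assessment are what the triple-blind claim leads a reader to rule out.

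**Working it through.** **1. The plan's own figure.** Inputs from Sample size: 46.7% and 78.6% RD, alpha 0.05, power 80%, 20% loss, 1:1. Mean rate p = (0.467 + 0.786)/2 = 0.6265.

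n per arm = [1.96 × sqrt(2 × 0.6265 × 0.3735) + 0.842 × sqrt(0.467 × 0.533 + 0.786 × 0.214)]² / 0.319² = 34.9, so 35. Then 35/0.80 = 43.75, so 44 per arm and 88 in total. The stated 88 reproduces (two-sided, no continuity correction). This point does not affect it.

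**2. How much of the sequence is known before consent.** Oncologist one holds 17 numbers and knows 17 of 17 letters; oncologist two holds 15 and knows 15 of 15; the remaining 88 − 32 = 56 go to the other three. The known share is 100%. For comparison, if the list were hidden and only past letters were visible, the best guess would be right in about 75%, 71%, 68% or 67% of cases for fixed blocks of 2, 4, 6 or 8. The article states no block size, so those sizes are assumptions.

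**3. What the code reveals.** Two letters, 44 patients each. If someone links one letter to one cream for one patient, every code that person can see is decoded, the other arm by elimination. For a family physician that is her own patients; for an oncologist, the range held; for those with the data set, all 88. This assumes that the identification code sent to the family physician and the alphanumeric code in the data are the one defined under Sequence generation, the only such code the article describes.

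**4. Illustration of selection bias.** Suppose no treatment effect, 44 per arm and a mean RD rate of 0.6265. Steering moves the underlying risk apart by d between arms; d is assumed, since the documents give nothing on it.

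SE = sqrt(0.6265 × 0.3735 × 2/44) = 0.103. Type I error = Φ(−1.96 + d/SE) + Φ(−1.96 − d/SE).

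| d | d/SE | all five steer the same way | independent hunches |
|---|---|---|---|
| 0.05 | 0.485 | 7.7% | 5.5% |
| 0.10 | 0.970 | 16.3% | 7.2% |
| 0.15 | 1.454 | 30.7% | 10.1% |

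The last column takes five equal-sized oncologists, each favouring A or B with probability one half. The net shift is then d, 0.6d or 0.2d with probabilities 2/32, 10/32 and 20/32. For d = 0.10: (2/32) × 0.163 + (10/32) × 0.090 + (20/32) × 0.054 = 0.072.

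**The case against.** The best defence is that knowing a letter is not knowing a cream. Recruitment says the control cream closely matches Alantel in colour, container, weight and smell, and the blinding section says that investigators and patients do not know which they have. That stands. A reader might infer that the trial was unblinded from the start; the documents do not support that. The defence does not restore concealment, because a hunch about a letter is enough to steer enrolment.

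Other stronger readings also go too far:

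- *Every oncologist holds all 88 assignments.* The text gives each a range; the 88 are known collectively.
- *One unmasking necessarily reveals everyone.* It does so only if the meaning of the letter is shared or reaches someone with the full data set.
- *Some patients were assessed in the service holding the lists.* Patients without means to travel "will be offered the possibility of being followed up in the radiation oncology service". That is an offer, and nothing shows that it was taken up.
- *The oncologist ranges break the block scheme.* The cut at 17 cannot end a 1:1 block, but position 32 can in one continuous sequence, and no block size is given.

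On size, the 8%, 16% and 31% figures need all five oncologists to lean the same way, which is the extreme case when A and B are masked. The regression adjustment under Statistical methods could absorb part of an imbalance in measured predictors, but not in what a recruiter sees and does not record.

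**Conclusion.** The point holds. The article positively describes a procedure in which the enrolling oncologist knows the next group letter before consent, so this is not a detail left to a fuller document. All letters are known in advance to whoever recruits against them. The two-letter code makes the blind depend on nobody linking a letter to a cream, which weakens the triple-blind claim for a clinician-judged outcome.

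The size of any bias cannot be read from the documents. Under the assumed shifts, type I error runs from about 5.5% (5 points, independent hunches) to about 31% (15 points, unanimous steering). These figures show what the procedure permits; they do not show that steering happened.

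**What to change.** **For the design as described:**

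- The manufacturer, which already makes both creams, packs containers numbered 01-88 to the list.
- Each oncologist receives only the number range and dispenses the next number after consent.
- The list stays with someone already in the project or at the manufacturer who does not recruit, assess or analyse.
- The A/B letter comes out of the patient code, and the arm variable is merged after database lock.

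The cost is container labels, a rewritten allocation paragraph and a named list holder. No extra patients are needed.

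**For this trial:** Trial status says the study concluded in June 2023, so those steps are no longer available. If analysis is still pending, remove the letter from the analysis identifier. In either case, report that allocation was not concealed from the recruiting oncologists and that the two-letter code limits the triple-blind claim. Neither removing the letter nor stratifying the analysis by oncologist undoes selection at entry or anything an assessor already knew, so neither should be presented as a repair. The cost is a short recode and a paragraph in the limitations.
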